#### Depression

The CES-D depression scale is a short self-report scale designed to measure depressive symptoms [40]. It includes 20 items, all scored from 0 (zero) to 3 points resulting in the total score ranging from 0 (zero) to 60 points. Four items (#4, #8, #12, #16) are reversed before calculating the total score. If information is missing for more than 5 items, the total score will not be calculated. Otherwise, the sum variable is calculated as follows: the sum of the answered items is divided by the number of answered items, and the number thus obtained is multiplied by 20. The higher the total score is, the more depressive symptoms the individual experiences.

The CES-D is supplemented with the Global Seasonality Score (GSS) calculated from a modified version [54] of the original Seasonal Pattern Assessment Questionnaire (SPAQ) [55, 56], which is a self-report tool used to evaluate the magnitude of seasonal changes in mood, appetite, weight, sleep duration, social activity, and energy level.

#### Diet quality

Diet quality is assessed with the validated Finnish Index of Diet Quality (IDQ) [43, 44] instrument. It evaluates the implementation of a health-promoting diet and nutritional recommendations by using 18 questions about the consumption of whole grains, fat, vegetables and fruit, sugar, and dairy products, as well as a regular meal rhythm. Based on the responses, the diet is scored from 0 (zero) to 15, and a score of 10 or higher indicates a health-promoting diet. The IDQ can also be used as a continuous variable without a cutoff into a health-promoting or unhealthy diet.

Description of diet quality is supplemented with the 11-item Diet Frequency Questionnaire (FFQ) [57], which contains questions about the meal rhythm, menu planning, cooking at home, eating out or social eating, use of dietary supplements, and food security. The frequency of eating fatty fish, nuts, seeds, seed oils, and snacks (chips, cookies, icecream, etc.) was added to the questionnaire for more detailed information on the foods suggested to be associated with depression. The FFQ intakes of these items will be converted to daily frequency equivalents (DFE) which are calculated by allocating the proportional values to the original frequency categories with reference to a base value of 1.0, equivalent to “once a day” [58, 59].

#### Eating behavior and competence

The psychology of eating behavior, including the cognitive, behavioral, emotional, and social aspects of eating habits, is involved in individuals’ adherence to changes in their dietary habits. The Three-Factor Eating Questionnaire R18 (TFEQ-R18) evaluates cognitive restraint (6 questions), uncontrolled eating (9 questions), and emotional eating (3 questions) [46]. In this study, from the point of view of the depressed individuals, emotional eating referring to a tendency to eat in response to negative emotions is more relevant in comparison with cognitive restraint and uncontrolled eating as supported by the association between depressive symptoms and emotional eating [60–63].

Responses of TFEQ-R18 are scored on a 4-point scale; the mean values are calculated for each factor, and these are subsequently transformed to correspond to the total score of 0 (zero) to 100. The results are calculated as a percentage of the highest possible value, between 0 and 100%, with higher values indicating greater engagement in the behavior. The higher the value is for each factor, the more likely it is to affect eating behavior.

In addition to the TFEQ-R18, eating competence is measured with the 16-item Satter Eating Competence Inventory (ecSI 2.0™) instrument [45] based on the Satter Eating Competence Model (ecSatter) [64, 65]. ecSatter is a biopsychological model designed for use in nutrition education and the characterization of eating attitudes and behavior. In adults [66] and adolescents [67], eating competence is associated with higher diet quality.

ecSI 2.0™ evaluates 4 dimensions related to food and eating. First, eating attitudes (5 items) comprise a positive, relaxed, and flexible interest in food and eating and a responsive attunement to the inner and outer experiences relative to eating. Second, food acceptance (3 items) means cognitive and behavioral processes and external influences of learning to accept and like a variety of foods, including new foods. Third, internal regulation of food intake (3 items) refers to the experiential processes of hunger, appetite, and satiety. Fourth, management of eating context (5 items) prioritizes the structure and meal planning as well as permission to eat adequate amounts of the preferred food at predictable times [45, 66]. All items are scored on a Likert scale and assigned values of 0 (zero) to 3. The scores of each subsection are summed up into an overall score of 1 to 48. The scoring follows the rationale of Garner [68]. The cutoff score for eating competence is 32 points.

#### Quality of life

The AQoL-8D [47] is a self-report questionnaire containing 35 questions which are grouped into 8 dimensions, including independent living, happiness, mental health, coping, relationships, self-worth, pain, and senses, which can be grouped into 2 super-dimensions: physical dimension and mental/physiological dimension. The scores on the AQol-8D both as a “psychometric” health-related quality of life (HRQoL) and a “utility” measure will be calculated with the scoring algorithms available via www.aqol.com.au. A simple psychometric score for health-related quality of life (HRQoL) is derived by adding the unweighted response order of each question with a total score of 35 to 177. Profile scores are calculated for the different dimensions. The AQoL-8D is also used as a “utility measure” for a cost-utility analysis requiring the computation of quality-adjusted life years (QALYs).

#### Work ability and functional capacity

The work ability and functional capacity questionnaire includes 3 modified questions focusing on the respondent’s work ability [48], including self-assessment of ability to work or study on a scale from 0 (zero) to 10 where 0 equals unable to work and 10 equals the best ability to work; evaluation of work ability in terms of the physical, physiological, and social requirements of the current job; and assessment of the probability of sustaining work ability until retirement age, and three 5-point scale questions about functioning in social situations, including loneliness [69], ability to do things together with others, and ability to confront strangers and address issues with them [70].

#### Economic evaluation

Two economic analyses will be carried out: a cost-utility analysis (CUA) [50] and cost-effectiveness analysis (CEA) [50]. Two ICERs will be calculated to evaluate the incremental cost per QALY (calculated from AQoL-8D scores) and the incremental cost per improvement in CES-D. An improvement is considered to occur if there is a 50% decrease in the CES-D depression scale score, which is a clinically relevant change, and also when the score falls below 12, 16, or 22 (“no depression”). The incremental cost-effectiveness ratio describes an extra cost in relation to an extra effect.

The viewpoint of the analyses does not cover the entire society, as has been recommended, because information on health care service use is not available for this analysis. The analysis will be conducted from the viewpoint of intervention providers, which includes the costs of the intervention such as the salaries of the staff with their ancillary costs, the costs of the facilities (room rental, nutrition guidance material), and the resources used by the participant for treatment (time, travel costs).

A number of sensitivity analyses will be carried out to assess the changes in variables and parameters with the greatest uncertainty or with the greatest impact on the total costs. Costs will be presented in 2020 prices in euros. Discounting is not needed due to the short run of the intervention.

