#### Secondary outcomes

The secondary outcomes (diet quality, eating competence, quality of life, work ability and functional capacity, cost-effectiveness) include the following:
Changes in the Index of Diet Quality (IDQ) [43, 44] from baseline to 12 monthsChanges in the Satter Eating Competence Inventory 2.0 (ecSI 2.0™) [45] and the Three-Factor Eating Questionnaire-R18 (TFEQ-R18) [46] from baseline to 12 monthsChanges in the Assessment of Quality of Life (AQoL-8D) [47] from baseline to 12 monthsChanges in the work ability and functional capacity questionnaire [48, 49] from baseline to 12 monthsThe difference in quality-adjusted life years (QALYs) between the intervention group and the control group.The incremental cost-effectiveness ratio (ICER) [50] as well as the incremental cost-utility ratio (ICUR) [50] of the intervention compared to the control group.

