### Sample size {14}

The total sample size of *n*=144 is based on the power calculation, when *α*=0.05, power=0.8, and effect size=0.5, and the estimated loss of participants is 15%. The calculation is based on the decline of 7 points assessed with the Center for Epidemiologic Studies Depression (CES-D) Scale.

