## Statistical methods

### Statistical methods for primary and secondary outcomes {20a}

The effects of the intervention on the primary and secondary outcomes will be analyzed following the intention-to-treat (ITT) principle. Group differences will be estimated using linear mixed effects models which allow considering the nested dependency structure generated from small groups and small group counselors in the data. All tests will be conducted using an alpha level of 0.05 and reporting 95% confidence intervals. Statistical analysis will be performed using the R software [72] and IBM SPSS Statistics® (IBM Corp., Armonk, NY, USA).

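### The ICER and ICUR are secondary outcomes assigned to a linear mixed model that can estimate only their components, and the stated sensitivity analyses do not carry sampling error into the cost-effectiveness result

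*Protocol article*

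**What the plan says.** - **Secondary outcomes** lists, as one item, "The incremental cost-effectiveness ratio (ICER) [50] as well as the incremental cost-utility ratio (ICUR) [50] of the intervention compared to the control group". The item just before it is the between-arm difference in QALYs.
- **Statistical methods for primary and secondary outcomes {20a}** covers all primary and secondary outcomes under intention to treat: "Group differences will be estimated using linear mixed effects models which allow considering the nested dependency structure generated from small groups" and small-group counselors. It adds: "All tests will be conducted using an alpha level of 0.05 and reporting 95% confidence intervals". It makes no exception for the economic outcomes.
- **Economic evaluation** plans the two ratios: "Two ICERs will be calculated to evaluate the incremental cost per QALY (calculated from AQoL-8D scores) and the incremental cost per improvement in CES-D". Improvement in CES-D is a yes/no criterion there. On uncertainty it says: "A number of sensitivity analyses will be carried out to assess the changes in variables and parameters with the greatest uncertainty", and the sentence goes on to include those with most influence on total costs.
- **Abstract (Discussion)** and **Dissemination plans {31a}** make implementation in health care conditional on the intervention being cost-effective and acceptable.

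**The concern.** Read together, the sections promise a mixed-model estimate and a 95% interval for two quantities to which that model cannot be fitted. No participant has an ICER; it exists only once the arms have been compared on cost and on effect. A negative ratio is also ambiguous: it can mean cheaper and better, or dearer and worse.

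The economic section does not close the gap. Varying inputs shows how the answer moves with assumptions. It does not show how far the answer could move because only some 122 people are analysed, or because they were treated in small groups.

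At stake is the precision attached to the cost-effectiveness objective, on which the article conditions implementation.

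**Working it through.** **1. The plan's own sample size.** Sample size {14} gives alpha 0.05, "power=0.8, and effect size=0.5, and the estimated loss of participants is 15"%, and "The calculation is based on the decline of 7 points assessed with the Center for Epidemiologic Studies Depression (CES-D) Scale". The implied SD is 7/0.5 = 14. Two-sided alpha is assumed, since sidedness is not stated.

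n per arm = 2 × (1.960 + 0.842)² / 0.5² = 62.8, so 63 per arm and 126 in total. 126 × 1.15 = 144.9, which agrees with the stated 144 to within one participant. (Dividing by 0.85 instead gives 149.)

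After 15% loss, 72 × 0.85 = 61 per arm, with power 0.79 at effect size 0.5. I use 61 per arm below.

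**2. When a ratio has a bounded interval.** Write ΔC and ΔE for the cost and effect differences. The Fieller 95% set for R = ΔC/ΔE holds all R with |ΔC − R·ΔE| ≤ 1.96·SE(ΔC − R·ΔE). This is a quadratic in R with leading coefficient ΔE² − 1.96²·SE(ΔE)². The set is a bounded interval only if that coefficient is positive, that is, if |ΔE|/SE(ΔE) > 1.96. With true difference δ:

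P(unbounded) = 1 − [Φ(δ/SE − 1.96) + Φ(−δ/SE − 1.96)].

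**3. Continuous effect.** In SD units SE = √(2/61) = 0.181. At 0.5, δ/SE = 2.76 and P(unbounded) = 21%. At 0.4 it is 40%, at 0.3 62%, at 0.2 80%. It passes 50% when δ falls below 1.96 × 0.181 = 0.355.

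**4. Responder effect, as the CES-D ratio uses.** The control rate is not given; 20-50% is assumed. A shift of 0.5 SD gives an intervention rate p₁ = Φ(Φ⁻¹(p₀) + 0.5), with SE = √{[p₀(1−p₀) + p₁(1−p₁)]/61}. This treats improvement as one generic criterion. The last column assumes an ICC of 0.05 (none is given) and 7 × 0.85 = 5.95 analysed per small group, so the design effect is 1 + 4.95 × 0.05 = 1.25.

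| Control rate | Intervention rate | Unbounded, no clustering | Unbounded, ICC 0.05 |
|---|---|---|---|
| 20% | 36.6% | 45% | 54% |
| 30% | 49.0% | 41% | 50% |
| 40% | 59.7% | 40% | 49% |
| 50% | 69.1% | 41% | 50% |

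The continuous figure at 0.5 rises from 21% to 30% with the same ICC. For an underlying shift of 0.3 SD the responder figure is 74-77% without clustering. The limit of 0.355 in step 3 applies to the effect measure actually in the denominator. Because dichotomising loses information, a responder ratio reaches 50% at an underlying CES-D shift of about 0.44-0.47 SD.

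**5. QALY ratio.** The article gives no QALY SD or expected gain, so both are assumed; SE = SD × 0.181.

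| True gain | SD 0.10 | SD 0.15 | SD 0.20 |
|---|---|---|---|
| 0.03 | 62% | 80% | 87% |
| 0.05 | 21% | 55% | 72% |
| 0.08 | 1% | 16% | 40% |

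**6. Wrong sign of the denominator**, Φ(−δ/SE): at the planned 0.5, 0.3% (continuous) and 1.3-1.9% (responder). At 0.2, 13% (continuous) and 19-21% (responder).

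**The case against.** The strongest reply is that the mismatch is one of wording. The statistical section speaks of group differences, and an ICER is built from group differences that the model can estimate. The economic evaluation has its own section, and no test of a ratio is announced. The QALY difference is a separate secondary outcome and gets a model and a 95% interval. Bootstrap methods, acceptability curves and willingness-to-pay thresholds usually belong to an analysis plan that is not shown.

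Much of this stands. The absence of those methods from a journal article is not a finding. The sensitivity analyses are not confined to costs. A reader might infer three stronger things, which the documents do not support:

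- **That cost-effectiveness will be decided on two point ratios.** No decision rule or threshold is stated, and the QALY difference is reported separately.
- **That the interval is usually unbounded at this sample size.** At the planned effect, without clustering, it is unbounded in fewer than half of trials.
- **That the conclusion would be sampling noise.** At the planned effect the denominator has the wrong sign in under 2% of trials.

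Nor can one say that nearly all the uncertainty lies on the QALY side: that needs a cost standard error and a willingness-to-pay value that the article does not give.

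What the reply does not remove is that the ratios are named secondary outcomes under a method that does not fit them, and that an interval for the QALY difference alone is not an interval for cost-effectiveness.

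**Conclusion.** The point holds in a limited form. The statistical section's method cannot be applied to the ICER and ICUR themselves, and the uncertainty method stated in the economic section leaves out sampling error and small-group dependency.

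The size depends on the effect. At 61 per arm and effect size 0.5, the ratio has no bounded 95% interval in about 21% of trials for a continuous effect and 40-45% for a responder effect, or 30% and 49-54% at an assumed ICC of 0.05. Without clustering, it exceeds half only if the true standardised effect on the measure in the denominator is below about 0.35. For the cost per QALY, the range of 1-87% mainly shows that the article does not supply the inputs.

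These figures assume two-sided alpha, 15% loss and normal approximations; the responder rates, QALY inputs and ICC are also assumed. This is a correction worth making while the analysis can still be specified; it does not invalidate the economic evaluation.

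**What to change.** - **Statistical methods {20a}:** exempt the ICER and ICUR from the mixed model and from the sentence on tests and intervals. State that they are descriptive ratios of the modelled cost and effect differences.
- **Economic evaluation:** for each participant compute λ × QALY − cost over a stated range of willingness-to-pay values λ. Estimate the between-arm difference (incremental net monetary benefit) with the same intention-to-treat mixed model, including small group, with baseline AQoL-8D utility as a covariate. Report it with its 95% confidence interval at each λ.
- Keep the parameter sensitivity analyses as an addition.

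No new data collection is needed: the AQoL-8D is scheduled at baseline and every follow-up, and the cost items are already in the assessment table. The price is some programming, a choice of the range of λ, and a rule for sharing group-session costs among participants. If small groups are resampled, for example to draw a cost-effectiveness plane, the result rests on only about 9-12 groups per arm (72/8 to 72/6). The cost-effectiveness statement will look less certain than a single ratio.

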#### Treatment expectancy

Treatment expectations can influence the intervention outcome. Thus, treatment expectations will be evaluated with the 6-item Treatment Expectancy Questionnaire [51]. It examines the extent to which participants believe that the treatment will help. Four questions are related to thinking, and two are related to feeling. Standardized scores will be used due to measures with 2 different rating scales (1 to 9 and 0 to 100%).

#### Acceptability

Acceptability [52] can have an impact on the treatment outcome and is therefore taken into account in this study. The acceptability of the Food for Mind group intervention will be evaluated with a self-evaluation questionnaire based on the Theoretical Framework of Acceptability (TFA) [52]. According to Sekhon et al., TFA is a multi-faceted construct that reflects the extent to which people delivering or receiving a healthcare intervention consider it to be appropriate, based on anticipated or experimental cognitive and emotional responses to the intervention. In TFA, the 7-component construct of acceptability is represented as follows: (1) affective attitude (“how an individual feels about the intervention”), (2) burden (“the perceived amount of effort that is required to participate to the intervention”), (3) ethicality (“the extent to which the intervention has a good fit with an individuals’ value system”), (4) intervention coherence (“the extent to which the participant understands intervention and how it works”), (5) opportunity costs (“the extent to which benefits, profits or values must be given up to engage in the intervention”), (6) perceived effectiveness (“the extent to which the intervention is perceived as likely to achieve its purpose”), and (7) self-efficacy (“the participants’ confidence that they can perform the behavior(s) required to participate in the intervention”). In addition to the acceptability questionnaire, personal feedback on the solution-focused facilitation of 6 group meetings will be collected by 5 questions adapted from Sharry [71]. All questions are scaled from 1 (completely disagree) to 5 (completely agree).

#### Weight and body composition

Weight (kg), BMI (kg/m^2^), body fat (%), and fat-free body mass (kg) are measured with the InBody 720 body composition analyzer (Manufacturer InBody Co., Ltd., Korea), which utilizes the bioelectrical impedance analysis (BIA) method.

### Plans to promote participant retention and complete follow-up {18b}

To promote participant retention, the research dietitian and control group counselor will remind participants before each group meeting by sending personal emails or a message to their WhatsApp groups. The research dietitian will send personal SMSs to the participants to remind them of the study follow-up appointments.

### Data management {19}

Data collected in paper format will be stored in a locked cabinet in a secure facility at the University of Eastern Finland and will only be accessible to the authorized research personnel. Data collected electronically will be stored (in a re-identifiable format) on servers securely housed and managed by the University of Eastern Finland. Any transmission of web-based data is encrypted. All data will be stored on a private, firewall-protected network. Study personnel will be given individual user IDs and passwords. Access will be restricted on a role-specific basis. After completing data cleaning measures, the database will be closed. All data will be exported to appropriate software to enable statistical analysis.

### Confidentiality {27}

All study data and research results are processed in line with the EU General Data Protection Regulation (679/2016). The confidentiality and anonymity of all personal data will be ensured throughout the study.

Each participant will be given a numeric identification code, which will be used to identify their data. The list of participants with their identification codes will be stored electronically on the university’s servers and will be password-protected. The results of this study will be analyzed and reported at the group level. Individual participants cannot be identified from the results.

Research data and documents will be stored for 6 years, after which they will be destroyed either by shredding the paper files or deleting electronic files. Data collected based on consent will not be used in subsequent studies.

### Plans for collection, laboratory evaluation, and storage of biological specimens for genetic or molecular analysis in this trial/future use {33}

Not applicable; no specimens were collected.

## Statistical methods

### Statistical methods for primary and secondary outcomes {20a}

The effects of the intervention on the primary and secondary outcomes will be analyzed following the intention-to-treat (ITT) principle. Group differences will be estimated using linear mixed effects models which allow considering the nested dependency structure generated from small groups and small group counselors in the data. All tests will be conducted using an alpha level of 0.05 and reporting 95% confidence intervals. Statistical analysis will be performed using the R software [72] and IBM SPSS Statistics® (IBM Corp., Armonk, NY, USA).

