#### Intervention description {11a}

Both the FM intervention groups and the BGM control (befriending) groups meet 6 times (5 1.5-h sessions and 1 3-h session) over an 8-week period. Each group has 6 to 8 participants. For social peer support, both groups will have their own WhatsApp groups, in which participants can share their own experiences and findings. The WhatsApp mobile application is used during the intervention and for the subsequent 10 months. Both groups continue their usual treatment for depression (treatment as usual) during the study.

A written manuscript prepared for every FM group meeting drawn up together in collaboration with a behavioral scientist helps the research dietitian to stick to a cohesive plan when instructing the group. The implementation of the BGM group meetings is also harmonized by the same instructor.

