SFT focuses on the present circumstances, desired future, possibilities, goals, progress, and strengths [39]. The person’s sense of autonomy is enhanced by placing the responsibility for a change in the hands of individuals by giving them an opportunity to choose and set their own goals and the means used to achieve these goals. Paying attention to the individual’s skills and potential increases his/her sense of competence, and this combined with respectful and patient-centered empowering language enhances feelings of relatedness.

By utilizing basic counseling skills, including presence and listening, genuineness, empathy, positive regard, and reflection, a counselor promotes the client’s motivation, readiness, willingness, and ability to take more responsibility for his/her personal well-being and improving dietary habits.

The topic of each of the six group meetings, including activities, assignments, and actions aiming to enhance the participants’ sense of autonomy, competence, and relatedness, is described in Table 1. In summary, each meeting includes discussions on the topic of the session; action-based methods, such as grocery shopping, cooking, eating together, and using all senses; and completing home assignments aiming to elucidate how the participants can improve their diet quality in their daily lives in practice. Each new meeting starts with the participants providing feedback on their experiences and positive changes, if any, in their eating habits resulting from completing the home assignments. In each group meeting, participants receive printed counseling material and assignments related to the day’s topic. The material and assignments aim to support the group participants to observe their eating behavior and practice mindful eating to identify hunger and satiety and pinpoint how they are feeling. The intervention group sessions are facilitated by the research dietitian. The protocol of each nutrition counseling meeting is presented in Additional file 1 (see Additional file 1).

**Table 1 Tab1:** Activities, assignments, and actions to enhance participants’ sense of autonomy, competence, and relatedness

Meeting topics and learning objectives (LO)	Activities	Home (HA) and WhatsApp (WA) assignments	Sample actions to enhance the sense of autonomy, competence, and relatedness

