#### Control group

The BGM control group follows a befriending protocol [34] and has a visit schedule identical in its content and length with the FM intervention group. The befriending group consists of a discussion of neutral topics of interest, such as hobbies, music, and sports, and engaging in activities together, with the intention of keeping participants engaged and in a positive mood. Befriending groups are facilitated by a rehabilitation counselor from a non-profit association (Turvalinkki ry), which organizes activities open for anyone with a focus on considering the needs and wishes of mental illness rehabilitees.

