### Assignment of interventions: allocation

#### Sequence generation {16a}

Participants will be randomized either into the FM behavioral nutrition intervention group (*n*=72) or the BGM control (befriending) group (*n*=72) in a 50:50 ratio using block randomization, which is a commonly used technique in clinical trial design [53].

Each pair of the starting intervention and control small groups (*n*=12–16) will form one block. A random study number between 1000 and 9999, and a number coding the treatment (0 = control, 1 = intervention) will be generated with Microsoft Excel for each study participant. Treatment numbers will be generated in a way that ensures that the setup becomes balanced.

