#### Concealment mechanism {16b}

To prevent forehand knowledge of the allocation sequence, randomization is done separately for each block (*n*=12–16) after obtaining the participants’ consent and conducting baseline assessments. With this procedure, the aim is to ensure that prior information does not selectively influence the choice of subjects.

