The process of recruiting study participants for a randomized clinical trial has been found to be challenging in the population of individuals with depression [75], as was also found in a randomized controlled SMILES trial of dietary improvement for adults with major depression [28]. Group activities are increasingly used in the treatment of depression in health care but may be too demanding for some persons with depression. Therefore, the group sizes of this study are kept suitably small. In addition, the subjects’ thoughts about the suitability of the group intervention to them and their readiness about participating are discussed in the first meeting with the research dietitian. Further, the health care staff may be unfamiliar with nutrition care as part of the treatment of depression, and recruiting eligible patients for the study may require a particular interest in bringing up the topic of participation in the study. To facilitate the recruitment, we have produced material to be used in recruiting staff. Moreover, the randomization of participants to the intervention and control groups might discourage some patients from participating in the study, even though they will get an option to have social peer support in the control group, to take part in one nutrition meeting, and get all the printed material at the end of the study.

The course of research has been delayed for more than 6 months because of the global COVID-19 pandemic. The priority of outpatient care units has been on primary care, which has limited the time left for recruiting patients. In addition, national restrictions to group gatherings and the closure of research facilities due to the pandemic have caused an interruption to recruitment and running group sessions. The strengths of this study include the study design (RCT) and the recruitment of study participants in collaboration with outpatient care units confirming the participants’ depression diagnosis and ongoing treatments. Moreover, the study utilizes behavior change theories as applied in a strength-based counseling method to achieve improvement in diet quality, and the effect of social peer support is controlled with the “befriending” control group.

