## Trial status

Recruitment began on 1 February 2018, and it will be continued until the end of 2022 (protocol version 2).

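### The randomization block (paired FM and BGM groups) is missing from the dependency structure named for the mixed models; if recruitment waves differ, the test of the arm effect is conservative

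*Protocol article*

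**What the plan says.** - **Block.** Under Sequence generation {16a}, "Each pair of the starting intervention and control small groups" forms one block of 12 to 16 people. Under Concealment mechanism {16b}, "randomization is done separately for each block", after consent and baseline assessment. A block is therefore a recruitment wave, with the two arms balanced inside it.
- **Number of blocks.** Intervention description {11a}: "Each group has 6 to 8 participants". With 72 per arm this gives 72/8 = 9 to 72/6 = 12 blocks.
- **Analysis.** Statistical methods {20a} proposes linear mixed models that can take account of the "nested dependency structure generated from small groups and small group counselors in the data". Block, pair, wave or start date is not named as a model term anywhere in the article.
- **Counselors.** FM: "The intervention group sessions are facilitated by the research dietitian". BGM: "Befriending groups are facilitated by a rehabilitation counselor from a non-profit association".
- **Calendar span.** Trial status: "Recruitment began on 1 February 2018, and it will be continued until the end of 2022". The Discussion adds that pandemic restrictions and closures "have caused an interruption to recruitment and running group sessions".

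**The concern.** Pairing one FM with one BGM group in each wave means that whatever is common to a wave cancels in the comparison of arms. The analysis gains from this only if the model knows about the pairs. Small groups are wholly inside one arm and counselor runs along arm, so neither named term separates a wave effect from a group effect. A random intercept for small group then absorbs the wave variance and treats the two groups of a pair as independent.

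A wave effect on the primary outcome is plausible here, because some waves were followed up before the pandemic interruption and others during or after it. At stake are confidence intervals that are too wide and lost power in a superiority trial planned at 80% power.

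**Working it through.** **The plan's own figure.** Sample size {14} gives α = 0.05 (taken as two-sided), power 0.80, effect size 0.5, 15% loss and N = 144; 7 points at d = 0.5 implies an SD of 14. Per arm, 2 × (1.960 + 0.842)² / 0.5² = 62.8, so 63. Inflated, 2 × 63 × 1.15 = 144.9, which agrees with 144. With 72 × 0.85 = 61.2 completers per arm, power is 0.79. The calculation has no group or wave term.

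**Formula.** Let K be the number of blocks, m the completers per small group, and w, g and e the shares of total variance due to wave, small group and residual (w + g + e = 1). The wave effect cancels within a pair, so

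- true variance of the arm contrast: (2/K)(g + e/m)
- variance that a groups-only model estimates: (2/K)(w + g + e/m)

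**Inputs.** From the article: K = 12 with m = 6 × 0.85 = 5.1, or K = 9 with m = 8 × 0.85 = 6.8. Assumed, because the article gives neither: g = 0.02, and w from 0 to 0.10.

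**Worked example, w = 0.05, e = 0.93.**

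- K = 12: e/m = 0.182. True SE = √[(2/12)(0.202)] = 0.184; groups-only SE = √[(2/12)(0.252)] = 0.205; ratio 1.12.
- K = 9: e/m = 0.137. True SE = √[(2/9)(0.157)] = 0.187; groups-only SE = √[(2/9)(0.207)] = 0.214; ratio 1.15.

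**Simulation.** Small-group means, 200,000 runs per setting. The groups-only analysis is an unpaired t test on 2K − 2 degrees of freedom; fixed block is a paired t test on K − 1. Power is at d = 0.5. Each cell shows 12 blocks / 9 blocks.

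| Wave share w | SE ratio | Type I error, groups-only | Power, groups-only | Power, fixed block |
|---|---|---|---|---|
| 0 | 1.00 / 1.00 | 0.051 / 0.050 | 0.72 / 0.69 | 0.68 / 0.63 |
| 0.01 | 1.02 / 1.03 | 0.046 / 0.043 | 0.71 / 0.67 | 0.68 / 0.64 |
| 0.02 | 1.05 / 1.06 | 0.040 / 0.039 | 0.70 / 0.66 | 0.69 / 0.64 |
| 0.05 | 1.12 / 1.15 | 0.031 / 0.028 | 0.66 / 0.60 | 0.70 / 0.65 |
| 0.10 | 1.23 / 1.29 | 0.019 / 0.016 | 0.60 / 0.52 | 0.72 / 0.67 |

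Type I error with fixed block was 0.049 to 0.051 throughout. The power curves cross at a wave share of about 2-3%. Power is below 0.80 even at w = 0 because of the assumed group share and the few degrees of freedom; that is a separate matter.

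A second simulation (40,000 runs, 5 or 7 completers per group, small-group variance not allowed below zero) agrees in direction and size. Groups-only type I error was 0.028 / 0.024 at w = 0.05 and 0.019 / 0.014 at w = 0.10. Power was 3-5 and 11-15 points below fixed block. Fixed block itself ran at 0.037-0.039 there.

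**Random block intercept.** With the block variance truncated at zero, it was estimated as zero in 38-50% of runs at w = 0 to 0.02, and type I error was 0.058 to 0.065. This was with K − 1 degrees of freedom when the block variance was positive and 2K − 2 when it was zero. Power at w = 0 was 0.74 / 0.71, part of which is bought by the inflated error.

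**The case against.** **The section is a summary, not a model.** It says what mixed models allow, and gives no fixed effects, time term or baseline covariate. It also leaves out treatment expectancy, which the Outcomes section says will enter the analysis. A fuller plan could add the block, and nothing in the article forbids it. This stands in part: a reader might infer that the block has been ruled out, and the text does not say so. But the section does state which dependency the models will consider, and it leaves out the one that the randomization created. A model fitted to that description would have the fault shown.

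**Seasonality.** A reader might point to the years of recruitment and the Seasonal Pattern Assessment Questionnaire as evidence of large wave effects. The document does not support this for the primary outcome. Baseline and 12-month visits fall at the same time of year, so a stable seasonal effect largely cancels in the change. The questionnaire is given once, at baseline, and describes persons rather than waves. Season bears more on the 8-week and 6-month outcomes. For the primary outcome the pandemic is the better argument, and its effect is not quantified.

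**There may be no wave variance.** Then nothing is lost, and a fixed block factor would itself cost power. This stands, and it makes the size conditional.

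**Conclusion.** The concern holds in conditional form. Blocks are part of the randomization and are not in the named dependency structure, and the terms that are named cannot replace them. If waves differ in 12-month CES-D change, the standard error is overstated and the test is conservative. A wave share of 1-2% makes this minor; 5% or more makes it worth several points of power, up to 12-15 at 10%. These figures rest on assumed wave shares, a 2% small-group share, 15% dropout and balanced groups of 6 or 8.

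Two stronger readings are not supported. One is that the trial's standard error is certainly too large, since the document gives no wave variance. The other is that the result would be biased or prone to false positives, since the estimate is unaffected and the error runs the other way.

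**What to change.** Name the randomization block (pair or wave) as a term in the primary and secondary models, with small group nested within block and arm, and fix its form before the recoded data are analysed.

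- **Fixed block factor.** Keeps type I error at 5% in the group-means check. It costs 8-11 degrees of freedom, and about 4-6 points of power if waves explain nothing.
- **Random block intercept.** Avoids that loss, but with 9-12 blocks it needs a small-sample correction or a block variance that may go negative. Truncation at zero gave about 6% type I error at wave shares of 0-2% even with degrees of freedom matched to the fitted model. In balanced data an unconstrained variance restores 5%, but then reproduces the paired test and its power.

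Choose one form in advance and report the other as a sensitivity analysis. The change is one of wording. Block membership is set when each block is randomized, so it should be recoverable, although the article does not say that it is kept in the analysis data.
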